
### Risks and Benefits to Participants

Each participant had been informed orally, assisted by the pre-exercise assessment document used for assessing the risks of the intervention in the following section at the first meeting in the course of the description of the study and before each session in the familiarization and intervention phase. They were required to give their consent and to sign the document before entering each session.

Regarding physical exercise, one could have concerns about performing high-intensity training in older adults because some risk exists of an acute cardiovascular event. Examples are cardiac dysrhythmia up until sudden cardiac arrest, sudden pulmonary vascular congestion, when the heart cannot keep up with the physical exercise, collapse with risk of injury while falling down, and acute myocardial infarction. Although it is true that the relative risk is higher during the physical exercise session compared to rest, the absolute risk is still very low (Riebe et al., 2015). In fact, a meta-analysis of high-intensity training even in patients with cardio-metabolic disease indicates that the risk is low and that it is safe to conduct (Weston et al., 2014). A review by Rognmo et al. (2012) that investigated the risk among coronary heart disease patients found in a total of 129,456 h during moderate-intensity training one fatal cardiac arrest and in 46,364 h of high-intensity training two nonfatal cardiac arrests, but no myocardial infarctions, thereby also finding low risk. Goodman et al. (2011) concluded: “*In conclusion, the mean rate of adverse events during exercise testing, including individuals referred for clinical exercise testing, based on our review article of the literature is less than 0.3 fatal events per 10,000 tests and 2.9 nonfatal events per 10,000 tests. Higher rates are observed for nonfatal events, although the adverse event reported in this context varies from mild arrhythmias that are not considered life threatening, to serious ventricular arrhythmias associated with increased risk of sudden death*.” Because only apparently healthy participants and not cardiovascular patients are recruited, the risk might be even lower. High-intensity training has already been conducted in older adults and has come to be regarded as safe (Hwang et al., 2016). As dangerous as the complications sound, severe incidents are often preceded by warning symptoms (Riebe et al., 2015). Examples are pain in the chest or in the legs that is unfamiliar while performing physical exercise [feeling of a stinger (“burning muscles”) in the legs can happen, but it is usually not harmful], chest tightness or discomfort, vertigo, feeling of fainting, and problems with breathing. If regarded seriously, these indicators can foreshadow difficulties and prevent major incidents. In conclusion, adverse acute events can happen during the familiarization and intervention phase, but the risk is very low and the described complications are rare. In addition, the participant might experience fatigue immediately after exercise, with muscle soreness on the days following the physical exercise.

During the video game session, the possibility of feeling fatigue exists, especially because of eye movements during video gaming, which are usually transient and which are not harmful.

Related to the fMRI, the possibility exists of feeling tired while performing the cognitive task. The participant might feel uncomfortable because of the loud background noise of the machine or the possible feeling of constriction because of the lack of space.

### Sample Size

Calculation of the sample size is not possible because no similar study has been reported to date. Soares et al. (2016) report that the optimal sample size for adequate reliability and power in fMRI studies might be between 16 and 32 participants. Zysset et al. (2007), who also conducted an experiment with Stroop task in fMRI, respectively used 23 and 24 participants per group. We also aim to include 24 participants.

### Interventions Overview

To check whether the participants can perform moderate to vigorous exercise and as already conducted in other studies (Knowles et al., 2015; Hwang et al., 2016; Grace et al., 2018), the participants will attend the familiarization phase over the course of 1 week and three sessions in all. Training at the first session is only performed at moderate intensity. The duration at high intensity is increased gradually for the second and third session. At the end of each session, the participants also practice the Stroop task and the video games for a total of 15 min. In the following intervention phase, each participant will sequentially perform four interventions with one intervention per week (four interventions after 4 weeks in all). The interventions are conducted once a week because reports of earlier studies state that to achieve a sufficient recovery in older adults, a break of at least 5 days is necessary between high-intensity physical exercise sessions (Herbert et al., 2015). Every intervention consists of a warm-up for the Stroop task to prevent the learning effect (Green et al., 2014). Each is followed by the actual physical exercise at either high or low intensity. After physical training, the participants go to the next room, where they can sit down and directly start the video gaming session with either the brain training video game “Brain Age” or with “Tetris.” The intervention is finished by the fMRI session using the Stroop task to investigate its related brain activity. Because there are two variables with two levels each, the possible combinations sum up to a sequence of four different interventions that one participant must undergo in a Latin square counterbalanced order (see Figures 1, 2). Each week, all participants will perform interventions one after another from morning until evening on two consecutive days. Participants are instructed to avoid strenuous physical activity during the 48 h (Knowles et al., 2015) preceding each intervention session. Each participant is also asked to refrain from food for 1.5 h and to have only a light meal beforehand, to refrain from caffeine and alcohol for 24 h (Knowles et al., 2015) before each intervention. Participants are asked to maintain their current lifestyle and not to make any changes to their level of physical activity or diet (Coetsee and Terblanche, 2017b).

**Figure 2 F2:**
[figure not shown]
Timelines and phases of this study.

### Physical Exercise Intervention

Participants perform physical exercise on an ergometer cycle (DK-8718RP; Daikou Corp., Japan). To tailor the intensity of the physical exercise for each, each participant performs the peak performance test at the first meeting and the last session of the familiarization phase to ascertain the maximal heart rate (HRmax). The intensity of the cycle ergometer has a range from level 1 until level 16. While cycling, the power is displayed in watts. In the beginning, the participant sits calmly on the cycle ergometer for 3 min and then starts to cycle. Initial mechanical power was set at level 1 for 2 min. the intensity was then increased by one level every 2 min until the limit of tolerance, with a fixed pedaling cadence of 60–70 revolutions per minute. The heart rate was displayed and recorded during each exercise session using a heart rate telemetry system (Polar H10 with app Polar Beat, ver. 2.5.2, on smartphone Freetel model FTJ17C00, Android ver. 7.1.2, retrieving data from online portal Polar Flow). At the end of every level, the participants rated their exhaustion on a Borg Rating of Perceived Exertion (RPE) Scale from 6 to 20 (Borg, 1982); the power will be recorded. Criteria used to end the exercise test stress were: (1) the inability to maintain the required pedaling cadence; (2) symptoms of fainting, vertigo, fatigue, dyspnea, or leg fatigue/pain; (3) achievement of age-predicted maximal heart rate, 208–0.7*age (Tanaka et al., 2001); and (4) rating of perceived exhaustion >18 on the Borg scale. The physical exercise is, if possible, always finished with a cool-down at lowest intensity for 3 min.

According to earlier studies that also conducted high-intensity physical exercise with older adults (Hwang et al., 2016; Coetsee and Terblanche, 2017b) the protocol for the physical exercise in the intervention phase is the following: starting with a warm-up for 10 min at 60% maximal heart rate (%HRmax), the bout is followed by 4 × 4 min intervals at 90%HRmax for high intensity or at 60%HRmax for low intensity, respectively, interspersed by 3 × 3 min intervals at 50%HRmax for active recovery. During the recovery bout, the participants rate their exhaustion during the previous bout on a Borg RPE Scale from 6 to 20 (Borg, 1982). The bout ended with a cool-down for 3 min at 50%HRmax. The protocol of the low-intensity bout instead of is continuous because it has been conducted as an active control in most studies. The present study is designed to mimic the interval character of the high-intensity bout to increase the similarity of experimental and control condition. To match the caloric expenditure of the high-intensity and low bouts, the period of time of each interval at 60% peak heart rate in the low-intensity bout is prolonged based on calculations incorporating the power at 60% and 90% peak heart rate from the peak power test of each. The total exercise period is 38 min for high intensity and 38–54 min for low intensity. The participants were instructed to maintain a cadence of 60–70 rpm, which was checked by the examiner. To avoid risks that might harm the health of the participants, the following criteria were used to interrupt the exercise: (1) symptoms of fainting, vertigo, fatigue, dyspnea or leg fatigue/pain; (2) reaching age-predicted maximal heart rate, 208–0.7*age (Tanaka et al., 2001); and (3) rating of perceived exhaustion >18 on Borg Scale. The physical exercise is, if possible, always finished with a cool-down at lowest intensity for 3 min (see Figure 3).

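### Borg ratings in the intervention bouts are scheduled only after each work interval, so the >18 stop criterion does not prompt a stop during work

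*Protocol article*

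**What the plan says.** All of this is in the protocol article, Methods, Physical Exercise Intervention.

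- **Intervention bouts, stop rule.** Three safety criteria interrupt the exercise: symptoms (fainting, vertigo, fatigue, dyspnea, leg fatigue or pain), reaching the age-predicted maximal heart rate (208 − 0.7 × age), and "3) rating of perceived exhaustion >18 on Borg Scale".
- **Intervention bouts, rating time.** One time is given: "During the recovery bout, the participants rate their exhaustion during the previous bout".
- **Peak performance test.** Here "At the end of every level, the participants rated their exhaustion", and "the intensity was then increased by one level every 2 min". The stop list for the test carries the same limit: "4) rating of perceived exhaustion >18 on the Borg scale".
- **Monitoring.** "The heart rate was displayed and recorded during each exercise session". In the intervention bouts, participants hold a set cadence, "which was checked by the examiner".
- **Durations.** "The total exercise period is 38 min for high intensity and 38–54 min for low intensity".

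**The concern.** A stopping rule works only as promptly as the information that feeds it. Here the perceived-exertion limit is meant to protect participants aged 60–70 working at 90%HRmax, but the rating is collected once the load has already dropped to recovery level and refers to effort that is over. Within an interval, stopping depends on the symptom criterion, the heart-rate display and whatever the participant chooses to report.

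The person who could be missed is one who is close to the limit and does not say so. The protocol already has a closer schedule in the peak test and does not carry it over to the intervention bouts. What is at stake is participant safety, to a limited degree. The sample size, error rate and planned models are untouched.

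**Working it through.** **Inputs** (Physical Exercise Intervention): warm-up 10 min; four work intervals of 4 min; three recoveries of 3 min; cool-down 3 min; peak-test level length 2 min; low-intensity total 38–54 min.

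**1. Reproduce the stated total for high intensity.**
10 + (4 × 4) + (3 × 3) + 3 = 10 + 16 + 9 + 3 = 38 min. This matches the protocol.

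**2. Place the ratings on that timeline (high intensity).**

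| Interval | Work (min) | What follows (min) | Scheduled rating |
|---|---|---|---|
| 1 | 10–14 | recovery 14–17 | in recovery, about interval 1 |
| 2 | 17–21 | recovery 21–24 | in recovery, about interval 2 |
| 3 | 24–28 | recovery 28–31 | in recovery, about interval 3 |
| 4 | 31–35 | cool-down 35–38 | none, read literally |

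Every scheduled rating follows the work it describes. A rating above 18 can therefore stop intervals 2, 3 or 4 before they begin, but not the interval in which that exertion occurred.

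**3. Compare with the peak test.** One rating per 2 min of work there; first prompt after 4 min of work here. 4 / 2 = 2 times the peak-test spacing.

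**4. Low-intensity bout.** Fixed parts: 10 + 9 + 3 = 22 min. Longest work interval: (54 − 22) / 4 = 8 min; shortest: (38 − 22) / 4 = 4 min. The range of 4–8 min assumes that the extra 0–16 min is spread equally over the four intervals.

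**5. Does the heart-rate criterion make the exertion limit redundant?** The heart-rate stop is the age-predicted maximum: 208 − 0.7 × 60 = 166 bpm at age 60, and 208 − 0.7 × 70 = 159 bpm at age 70. The work target is 90% of the participant's own HRmax from the peak test. That test can also end on cadence, symptoms or Borg above 18, so the measured HRmax can lie below the predicted value. Illustration with an assumed value: a 65-year-old whose test ended at 140 bpm works at 0.9 × 140 = 126 bpm, while the stop is 208 − 0.7 × 65 = 162.5 bpm, above that person's own measured maximum. For such a participant the heart-rate stop is unlikely to act, and interruption within an interval rests on symptoms or perceived exertion.

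The figures in steps 3 and 4 describe the spacing of prompts only. They are not evidence of harm.

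**The case against.** The case for leaving the text alone has several parts.

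- **No contradiction.** The criteria interrupt the exercise; the text does not promise a stop inside an interval. A recovery rating above 18 can end the session, and nothing bars a participant from reporting one during work. This stands: the criterion is delayed, not inert.
- **Other safeguards cover the interval.** Fatigue, dyspnea and leg fatigue stop exercise at any time, heart rate is displayed, an examiner is present, and participants are screened and complete three familiarization sessions. This stands in large part and is why the point is minor. It does not make the rating superfluous: fatigue is listed without a threshold although some is expected at 90%HRmax, Borg above 18 is the only graded exertion limit, and the heart-rate stop may sit above a participant's own maximum.
- **The peak test is a different exercise.** It climbs to the limit of tolerance, and its ratings also fall at stage ends. This is fair, so the twofold spacing is not a measure of risk. But in that test no recovery separates the levels, so the rating decides whether loading continues; in the intervention bouts the load has already been lowered.
- **Low intensity hardly matters.** Agreed. At 60%HRmax, the warm-up intensity, a rating above 18 is not a realistic concern. A common schedule is wanted there only to keep the two conditions alike.
- **An article may omit operational detail.** The rating time is not omitted; it is stated, and it fits the stop rule poorly. The Dissemination Policy says the article should serve as the full protocol. The same section also speaks of a full protocol that will not be made public, so little weight is put on that line.
- **Prompts could shorten more high-intensity bouts.** This is possible, but it would only enforce a limit the protocol has already set.

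**Conclusion.** The point holds as a minor safety improvement. The only scheduled rating in the intervention bouts looks back at a finished interval, so the >18 criterion does not prompt a stop during any of the four work intervals, and the fourth, read literally, is not rated at all. The delay to the first prompt is 4 min of work at 90%HRmax, against 2 min in the peak test.

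For high intensity the conclusion rests on the text and the stated durations alone. The 4–8 min low-intensity range needs the equal-spread assumption and carries little weight. No harm is shown and no stated analysis changes.

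**What to change.** In Physical Exercise Intervention:

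1. Have the examiner ask for the Borg rating once during each of the four work intervals, on the same schedule in high- and low-intensity sessions, for example 2 min into the interval, the spacing already used in the peak test.
2. State that a rating above 18, asked for or volunteered at any time, ends work and moves the participant to the cool-down. The volunteered part matters because a prompt at 2 min cannot capture the later part of the interval.
3. Keep the recovery rating as the record of the whole interval, and take it in the cool-down for the fourth.

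**Cost.** One or two sentences and a changed examiner script. The scale, the examiner and 2-min prompting are already in place. The downsides are a brief question during work and possibly some high-intensity bouts ended early under the existing limit.

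### The criteria for interrupting the exercise bouts leave out chest pain and chest tightness, which the protocol's own risk section names as warning symptoms; the peak test's symptom criterion has the same gap.

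*Protocol article*

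**What the plan says.** Three places in the protocol article bear on this.

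- **Risks and Benefits to Participants.** After listing acute cardiovascular events as possible complications, the section states that "severe incidents are often preceded by warning symptoms". It then gives examples: "Examples are pain in the chest or in the legs that is unfamiliar while performing physical exercise", followed, after a remark on harmless muscle burning, by "chest tightness or discomfort, vertigo, feeling of fainting, and problems with breathing". It adds: "If regarded seriously, these indicators can foreshadow difficulties and prevent major incidents".
- **Physical Exercise Intervention, intervention bouts.** The list opens with its purpose: "To avoid risks that might harm the health of the participants, the following criteria were used to interrupt the exercise". Criterion (1) is "symptoms of fainting, vertigo, fatigue, dyspnea or leg fatigue/pain". Criterion (2) is reaching the age-predicted maximal heart rate, and criterion (3) is a Borg rating above 18.
- **Physical Exercise Intervention, peak performance test.** Criterion (2) is "symptoms of fainting, vertigo, fatigue, dyspnea, or leg fatigue/pain". The others are loss of pedaling cadence, the age-predicted maximal heart rate, and a Borg rating above 18.

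**The concern.** The risk section argues that severe events tend to announce themselves and that heeding the signs is protective. The stop criteria are where that argument should become an instruction to the examiner. They pick up fainting, vertigo, breathing difficulty and leg pain, but no chest symptom.

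Participants are 60 to 70 years old and cycle in intervals at 90% of maximal heart rate. Strength and Limitations mentions medical supervision during the intervention only as something that would improve safety further. An examiner without a clinician present depends more on a complete written list. What is at stake is participant safety, not inference.

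**Working it through.** The plan states no figure on this point, so the check compares the texts.

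**Step 1: warning symptoms against the symptom criteria.**

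| Symptom in Risks and Benefits | Bouts, criterion (1) | Peak test, criterion (2) |
|---|---|---|
| Unfamiliar chest pain | absent | absent |
| Unfamiliar leg pain | present | present |
| Chest tightness or discomfort | absent | absent |
| Vertigo | present | present |
| Feeling of fainting | present | present |
| Problems with breathing | present (dyspnea) | present (dyspnea) |
| Catch-all for other symptoms | absent | absent |

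**Step 2: could another criterion in the lists act as a substitute?**

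- *Heart-rate ceiling.* The formula is 208 − 0.7 × age, which gives 208 − 42 = 166 at age 60 and 208 − 49 = 159 at age 70. The peak test that supplies each participant's maximal heart rate has the same ceiling among its end criteria. A bout held at 90% of that maximum therefore runs below the ceiling (at most about 0.9 × 166 = 149 at age 60 and 0.9 × 159 = 143 at age 70). Chest pain at the target intensity would not trigger it.
- *Borg rating above 18.* This measures exertion, not chest symptoms. In the bouts it is collected during the recovery interval, about the interval just finished.
- *Loss of cadence (peak test only).* This is a performance limit and can occur with or without chest symptoms.
- *Fatigue or dyspnea.* Chest symptoms may come with either, and the listed trigger would then apply. Isolated chest pain or tightness remains uncovered.

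**Step 3: does another section print a stop rule for chest symptoms?**

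- *Eligibility Criteria.* The PAR-Q+ and blood-pressure exclusions act before exercise.
- *Risks and Benefits to Participants.* Participants are informed orally with the help of a pre-exercise assessment document, which they sign before each session. The document is linked to the risks described in that section, but its content is not shown.
- *Research Ethics Approval and Informed Consent.* Participants may withdraw at any time. That is a right of the participant, not an instruction to the examiner.

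None of these is a printed criterion to stop for chest symptoms.

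**The case against.** The strongest reply is that conduct is probably safer than the text. A competent examiner would stop for chest pain, nothing in the protocol says to continue, and the signed document may tell participants to report exactly these symptoms. The risk section offers its symptoms as examples, and the stop lists do not claim to reproduce them. All of this stands, and it limits the point to the lists as printed. It does not remove the point, because the bout list is numbered, closed and introduced as the safety rule. Nor does it help much that this is a journal article: Dissemination Policy says the article should serve as the full protocol, and the issue is two complete lists that do not match the risk section, not detail left out for brevity.

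A second reply concerns the peak test. Its list is introduced as criteria for ending a test that runs to the limit of tolerance, and some items simply mark exhaustion. Only the bout list is expressly labelled a safety rule. That is fair, so the bout list carries the point and the peak test follows as the same omission.

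Three stronger readings are tempting, and the document supports none of them.

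- *That participants with chest pain would be made to go on.* No text says so.
- *That a fixed share of the warning symptoms is missing.* The share depends on whether pain in the chest or legs is counted as one item or two. The finding is that the chest symptoms are missing, however the items are counted.
- *That the omission carries a calculable event risk.* The quoted exercise-testing rates ("less than 0.3 fatal events per 10,000 tests and 2.9 nonfatal events per 10,000 tests") could be multiplied by the number of sessions. For 24 participants with two peak tests and two high-intensity bouts each, that is 96 × 2.9 / 10,000 = 0.028 nonfatal events. Adding the second and third familiarization sessions, which also contain high-intensity work, gives 144 × 2.9 / 10,000 = 0.042. Either way the result is background risk, taken from a population that includes people referred for clinical testing. It says nothing about how many events a chest-symptom criterion would avert.

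**Conclusion.** The point holds as a minor safety correction. The printed rule for interrupting the bouts omits chest pain and chest tightness or discomfort, although the protocol itself names them as warnings of severe incidents. The peak test's symptom criterion shares the omission, and neither list has a catch-all.

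The conclusion rests on reading the lists as complete, which their numbering and introduction support, and on the absence of any other printed stop rule for chest symptoms. If the signed pre-exercise document turns out to contain one, what remains is an inconsistency between documents.

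**What to change.** Add *chest pain, tightness or discomfort* to criterion (1) for the intervention bouts and to criterion (2) for the peak performance test, and to the examiner's checklist if one exists. Keep the existing triggers as they are. The cost is one phrase in each list and possibly a few more interrupted bouts; no new procedure, staff or change to the analysis is needed.
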